### Sample Size

Previous research by our group (48) estimated that for those receiving usual care, the mean number of health-care contacts with program providers per month is 4.6. It was hypothesized that the intervention group will have at least 25% more health-care contacts with program providers per month (mean = 5.8) during the critical transition period. Because the primary outcome represents a count variable, sample sizes for Poisson regression were calculated using the formula provided in Signorini (56). Sample sizes of 67 per group achieve 80% power to detect a rate ratio of 1.25 with a significance level of 0.05 using a two-sided test. However, we expect an attrition rate of 22.0% (44), thus the final sample size per group is inflated by 22%, resulting in a total of 172 study participants. A subsample of study participants (*n* = 22), service providers (*n* = 12), and other key informants (*n* = 6) was estimated a priori as adequate to achieve saturation of qualitative findings and triangulation of data sources.

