### Study Participants: Recruitment, Eligibility, and Randomization

The CATCH program receives 450–600 referrals of homeless adults per year, from hospitals or community agencies, prior to or shortly after hospital discharge for a mental health condition. Study participants were recruited among successive new CATCH program participants. Referrals to the study were made by CATCH staff during program intake meetings. Program participants expressing an interest in receiving information about the study were contacted by research staff to confirm interest, eligibility, to obtain informed consent, and to conduct a baseline assessment.

Study participants meet both CATCH program and CATCH-FI study eligibility criteria. Program eligibility criteria include: (1) current homelessness (defined as having no fixed place to stay for at least the past seven nights with little likelihood of finding a place in the upcoming month) or precarious housing (defined as currently occupying a single room in a multi-tenant building or house with shared common areas including bathroom and kitchen or a hotel/motel as a primary residence, and having a history of one or more episodes of absolute homelessness in the past year); (2) service provider-determined unmet mental health needs; (3) service user-determined unmet support needs; and (4) age 18 years or older. Excluded from the program are individuals with recent aggressive behavior requiring a higher intensity of support, or individuals whose illness severity necessitates residential care. To be eligible for the current study, in addition to meeting program eligibility requirements, participants must have been new referrals to CATCH, recently admitted or readmitted to hospital services, and have had at least one contact with the CATCH team.

Participants were randomized following the baseline interview using block randomization (55), which randomizes the participant list into groups 1:1 using blocks of four and six. This approach has the advantage of maintaining balanced group sizes throughout the recruitment process. The nature of the intervention precluded blinding of participants and study staff.

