##### Primary Outcome Analysis

Since program duration is customized for each participant, and may last between 1 and 6 months, we will calculate participants' person-months of program participation. This will allow us to estimate the rate ratio comparing the intervention and usual care groups with respect to the number of contacts with CATCH service providers per month. Therefore, for each participant, the total number of months in the program before discharge and the total number of contacts over the number of months in the program will be calculated. A Poisson regression model (PROC GENMOD) with total contacts as the dependent variable, group (CATCH-FI vs. CATCH-UC) as the covariate and an offset equal to the log (number of months spent on the program) will estimate the rate ratio and 95% confidence intervals, and the mean number of contacts per person-months and 95% confidence intervals in each group.

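### The stated 80% power with 67 per group matches a one-month Poisson count without over-dispersion, not the planned analysis of total contacts over 1 to 6 months

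*Protocol article*

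**What the plan says.** The Sample Size section takes its control rate from the group's earlier research, where under usual care "the mean number of health-care contacts with program providers per month is 4.6". It hypothesizes that the intervention group will have "at least 25% more health-care contacts with program providers per month (mean = 5.8"). It names the method: "sample sizes for Poisson regression were calculated using the formula provided in Signorini (56"). It then concludes: "Sample sizes of 67 per group achieve 80% power to detect a rate ratio of 1.25". The test is two-sided at the 0.05 level. The 67 is raised for attrition to 86 per group, 172 in total. The section states neither a length of observation per person nor an over-dispersion factor.

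The Quantitative Measures section counts the primary outcome over 6 months or until program discharge. Primary Outcome Analysis says that time in the program varies from 1 to 6 months. It fits a Poisson model to each person's total contacts with "an offset equal to the log (number of months spent on the program"). The negative binomial fallback for over-dispersed data appears only under Secondary Outcome Analysis.

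**The concern.** The power of a Poisson comparison depends on the expected number of events. That number is the monthly rate times the months observed, so a monthly rate alone does not fix the sample size. If 67 comes from treating 4.6 as each person's whole expected count, the calculation describes a one-month outcome that the trial does not analyse.

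Two omissions then pull in opposite directions. Longer observation adds information. Between-person variation in contact rates removes it, and longer follow-up does not average that variation away. Such variation is plausible here, because the article says that program length is customized and that contacts follow each person's needs and preferences.

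The 80% figure is the benchmark against which a null result would be read. If it belongs to a different analysis, readers cannot tell whether a null result argues against a 25% increase or whether the trial could not have shown one.

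**Working it through.** **Inputs from the article.** Control rate 4.6 per month, rate ratio (RR) 1.25, two-sided 0.05, 80% power and the Poisson-regression formula (Sample Size); 1:1 allocation (Study Participants); exposure of 1 to 6 months (Primary Outcome Analysis). Let T be mean months observed and φ an over-dispersion factor; the article states neither for the sample size.

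**Step 1: reproduce 67.** For a binary covariate with 1:1 allocation, the total is

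N = φ × (z₀.₉₇₅√4 + z₀.₈₀√(2 + 2/RR))² / (T × 4.6 × (ln RR)²)

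- Numerator, φ = 1: (1.960 × 2 + 0.8416 × √3.6)² = (3.920 + 1.597)² = 30.43
- Denominator, T = 1: 4.6 × 0.2231² = 4.6 × 0.04979 = 0.2290
- N = 132.9, or 66.4 per group, rounded up to **67**. Power at 67 is 80.3%.

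Other routes at T = 1 do not give 67. A one-sided test gives 53. Using 5.8/4.6 = 1.26 as the ratio gives 62, as do Wald, rate-difference and square-root methods. The attrition step also reproduces: 67/0.78 = 85.9, so 86 per group and 172 in total.

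**Step 2: same formula, exposure of the planned analysis (φ = 1).** Power = Φ[(√(134 × T × 4.6) × 0.2231 − 3.920)/√3.6], with 134 = 2 × 67.

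| Mean months T | Total N for 80% power | Power with 67 per group |
|---|---|---|
| 1 | 132.9 | 80.3% |
| 3 | 44.3 | 99.9% |
| 4 | 33.2 | above 99.9% |
| 6 | 22.1 | above 99.9% |

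**Step 3: allow between-person variation.** The negative binomial dispersion k is an assumption, shown as a range. With n per group and everyone observed for T months,

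SE² = [1/(4.6T) + 1/(5.75T) + 2k]/n, power = Φ(0.2231/SE − 1.960).

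At T = 4 the first two terms are 1/18.4 + 1/23 = 0.0978. For example, k = 0.2 and n = 86 give SE = √(0.4978/86) = 0.0761, and power = Φ(2.93 − 1.96) = 83%.

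| k (assumed) | Power, 67 per group | Power, 86 per group |
|---|---|---|
| 0.1 | 92% | 97% |
| 0.2 | 74% | 83% |
| 0.3 | 59% | 70% |
| 0.5 | 41% | 51% |

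**Step 4: where power crosses 80%.** Solve for k, with (1.960 + 0.8416)² = 7.849: k = [n × 0.04979/7.849 − 0.0978]/2.

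- n = 67: (0.425 − 0.098)/2 ≈ 0.16
- n = 86: (0.546 − 0.098)/2 ≈ 0.22

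Varying T from 3 to 6 months moves these limits only to 0.15–0.18 and 0.21–0.24. Once k is of this size, dispersion matters far more than exposure. At k = 0.5 and 4 months, the rate ratio detectable with 80% power is about 1.43 (67 per group) or 1.37 (86 per group).

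**The case against.** **Another pairing also gives 67.** N depends on φ/T, so any over-dispersion factor equal to the mean months observed (φ = 4 at 4 months, φ = 6 at 6 months) gives the same answer. This stands, and it is wrong to say that one month is the only possible basis. The one-month reading rests on the plain Poisson model that the article names for both the sample size and the primary analysis. The article states no φ that would support another pairing.

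**The monthly unit is open, and one month is conservative.** Both means are given per month, and the estimand is a monthly rate ratio. Under the planned Poisson model, using one month understates power. Both points stand. They do not make 80% the power of the planned analysis, and the surplus exists only if variation is purely Poisson.

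**Low power is not shown.** A reader might infer that the trial is underpowered. The documents do not support this: they give no dispersion, every k above is assumed, and with 86 per group power still exceeds 80% at k = 0.2.

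**Attrition.** A reader might also fault the 22% allowance because the primary outcome comes from charts. That does not hold. Participants may withdraw, the 172 also serve secondary outcomes from the 6-month interview, and the allowance only adds people.

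**Little can change now.** Recruitment is complete, the estimate and its interval are unaffected by the power statement, and a fuller protocol may hold the missing assumptions. This lowers the priority. It does not remove the mismatch between the published figure and the published analysis.

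**Conclusion.** The point holds in a limited form and should be fixed, though it does not threaten the trial's validity. Under the plain Poisson model that the article names, 67 per group with 80% power corresponds to one month per person and no over-dispersion, whereas the analysis uses 1 to 6 months of contacts. The stated 80% is thus not the power of the primary analysis, and the sign of the discrepancy cannot be settled from the article. At one end is near-certain detection under pure Poisson variation; at the other is about 51% with 86 per group at an assumed k of 0.5. The negative binomial figures rest on normal approximations, equal exposure of 4 months, the same k in both arms and all 86 (or 67) per group contributing.

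**What to change.** Keep the 172 participants and leave the published calculation as the record of how the size was chosen. Before the primary data are analysed, add a short restatement, labelled as made after recruitment, that gives:

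- the assumed mean months of exposure per person;
- the dispersion estimated from the earlier program data that supplied the 4.6, or a sensitivity range such as k = 0.1 to 0.5 if those data cannot supply it;
- the resulting power at a rate ratio of 1.25, or the rate ratio detectable with 80% power, for an analysis that allows over-dispersion (negative binomial or robust variance).

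The cost is one recalculated paragraph and no additional participants. The downside is that the stated power may become less favourable than 80%.

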### Data Collection

Baseline data collection occurred between November 2018 and September 2020; follow-up data collection will be completed in July 2021. All data collection is conducted by trained research assistants from the Survey Research Unit at the Centre for Urban Health Solutions at St. Michael's Hospital. Quantitative surveys lasting 1–2 hwere administered at baseline (up to within 6 weeks of enrollment) and are offered at 6 months post-enrollment (between 6 weeks prior to and up to 16 weeks after that) to all study participants. Survey data are collected using SNAP professional software, and data are held on an internally owned and operated secure sever. All program participants received honoraria paid in-person, by check or email money transfer for each completed interview ($30 for the baseline interview and $60 for the 6-month follow-up interview), in addition to public transportation fare.

Qualitative data collection occurred between April 2019 and December 2020. In-depth, 45–60-min semi-structured interviews were conducted during the study period with program participants and other key informants, and focus groups were conducted with CATCH service providers. Qualitative interview service user participants received an honorarium of $30 and public transportation fare.

This study uses several evidence-based follow-up and study retention strategies for this population (57, 58). To minimize attrition, participants were asked at baseline to provide detailed contact information for themselves and any family, friends, or service providers who could help locate them. To support study retention further, participants were also encouraged to call study staff monthly to update contact information (receiving a $10 honorarium per call). In addition, study staff regularly reach out to participants between interviews to maintain up to date contact records.

A schedule of enrolment, intervention, and assessment is detailed in Figure 1.

**Figure 1 F1:**
[figure not shown]
Schedule of enrolment, intervention, and assessments.

### Measures

#### Quantitative Measures

The primary outcome is service engagement, or program attendance, measured as a count of health-care contacts with CATCH service providers per month over the 6-month period (or until discharge from the program). CATCH service providers record program participant attendance in health care appointments and care planning meetings lasting at least 5 min in participant health records. Eligible health-care contacts include in-person and virtual appointments, as well as care planning conversations through email or text. This definition is consistent with the current program practices and ensures only eligible health-care contacts are recorded and reported to the funding agency. Data on program attendance will be captured at study end through chart reviews by a blinded study staff.

Demographic data and other participant characteristics including residential status and income sources were collected by self-report at baseline. Secondary outcome measures of mental and physical health status, health service use, quality of life, and housing are being collected at baseline and 6 months and a measure of perceived therapeutic working alliance is collected at 6 months. Health service use will also be evaluated using data linkage of administrative health records, conducted at ICES, which holds population-based health and health service use information at the patient level for all Ontarians with health insurance.

See Table 1 for a detailed description of all quantitative measures.

**Table 1 T1:** Description of measures.

**Domain**	**Instrument**	**Description of instrument**
**Service engagement**		
	Chart review	Number of contacts with CATCH service providers per month over 6 months or until discharge from the program. Contacts are calculated by considering the number of appointments attended, phone calls, texts, emails, no-shows, and cancellations and drop-outs. Synchronous interactions must last at least 5 min to be counted as meaningful, consistent with funder reporting requirements.

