### Study Design

Using a community-based, participatory research framework, CATCH-Financial Incentives (CATCH-FI) is a pragmatic field trial using mixed methods to evaluate the impact and acceptability of financial incentives in promoting service engagement of homeless adults with mental illness following hospital discharge. This study was launched in December 2018. Study recruitment is completed, data collection however is ongoing and the trial is registered with ClinicalTrials.gov (Identifier: NCT03770221).

CATCH program participants enrolled in the CATCH-FI trial and randomly assigned to the intervention arm receive $20 for every week they remain meaningfully engaged with program service providers over 6 months of follow-up, or until they are successfully transitioned to longer-term supports. Study participants can earn up to $80CAN per month by attending meetings with their program service provider by phone, text, email, or in-person, as per their care plan. Participants randomly assigned to the control arm receive usual CATCH care, which does not include a financial incentive for attending meetings with their program service provider.

The impact of financial incentives on participants' level of service engagement, measured by program attendance, evaluated as the number of “health-care contacts” a participant makes with CATCH service providers over a 6-month follow-up period. Of note, participant contacts with service providers are counted as “health-care contacts” if they relate to participants' care plans. As a low barrier program, CATCH service providers meet program participants in person, via phone, email, or texts, as per program participants' needs and preferences. Social or trivial contacts of program participants with service providers are not considered “health-care contacts” and are not being measured or documented in program records or reports to program funders.

Secondary health, health service use, quality of life, and housing outcomes (secondary outcomes) are also being collected over the study period. The study hypothesis is that participants receiving financial incentives will have higher levels of service engagement and consequently better health, health service use, quality of life, and housing outcomes compared to participants receiving usual care.

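### Table 1 lists no-shows, cancellations and drop-outs in the calculation of the primary contact count without saying how they enter, although the text defines the outcome as attendance

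*Protocol article*

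**What the plan says.** Three places in the protocol article define the primary outcome in words.

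- Study Design says engagement is "measured by program attendance, evaluated as the number of “health-care contacts” a participant makes with CATCH service providers". The incentive in the same section is earned "by attending meetings with their program service provider by phone, text, email, or in-person, as per their care plan".
- Quantitative Measures says: "The primary outcome is service engagement, or program attendance, measured as a count of health-care contacts with CATCH service providers per month". Providers "record program participant attendance in health care appointments and care planning meetings lasting at least 5 min", and the eligible types are then listed: "Eligible health-care contacts include in-person and virtual appointments, as well as care planning conversations through email or text". No missed event appears in that list. The section refers the reader to Table 1 for the detailed description of every quantitative measure and gives the counting to a blinded chart review at study end.
- Table 1, Service engagement row, says: "Contacts are calculated by considering the number of appointments attended, phone calls, texts, emails, no-shows, and cancellations and drop-outs". It then adds: "Synchronous interactions must last at least 5 min to be counted as meaningful".

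Primary Outcome Analysis takes total contacts as the dependent variable of a Poisson regression with log months in the program as offset. It does not say which contacts make up the total.

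**The concern.** A no-show, a cancellation or a drop-out is the opposite of attendance. Table 1 nevertheless places these events, with no sign or weight, in the same list as attended appointments, calls, texts and emails, in the sentence that says how the count is obtained. A chart abstractor could reasonably add them, subtract them or set them aside, and each choice gives a different primary dataset.

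The additive reading matters most. The incentive pays for attending, so one direct way it could work is by turning missed meetings into attended ones. If both kinds of event score one contact, that part of the effect disappears from the outcome. Even if the incentive leaves missed events alone, adding a similar number to both arms pulls the rate ratio towards 1.

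**Working it through.** **Inputs from the document (Sample Size).** Usual-care rate 4.6 contacts per month; rate ratio 1.25, so 4.6 × 1.25 = 5.75 per month with the incentive (printed as 5.8); two-sided 0.05; 80% power; 67 per group; 22% attrition; 172 in total. Allocation is 1:1.

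**Assumption.** The rate of missed events, m per month in usual care, is not given. I let it run from 0.5 to 4.6.

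**Step 1: reproduce the plan's figure.** Signorini's formula with half the sample in each arm, one month of exposure and no overdispersion is

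N = [z(0.975)·√V0 + z(0.80)·√V1]² / [rate · (ln RR)²], with V0 = 1/(0.5 × 0.5) = 4 and V1 = 1/0.5 + 1/(0.5 × 1.25) = 3.6.

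N = [1.960 × 2 + 0.842 × 1.897]² / [4.6 × 0.2231²] = 132.9, or 67 per group. Then 67/0.78 = 85.9, rounded up to 86 per group and 172 in total. Both stated figures reproduce, so the sample size is not in question here. Power with 134 participants is 80.3%.

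**Step 2: add missed events to the count.** The true gain in attendance is 5.75 − 4.6 = 1.15 per month. Let f be the share of that gain that comes from converting missed contacts into attended ones. Then

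RR = (5.75 + m − 1.15f) / (4.6 + m).

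Power uses the same formula, with 4.6 + m as the usual-care rate, the diluted RR and 134 participants:

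power = Φ{[√(134 × (4.6 + m)) · ln RR − 1.960 × 2] / √(2 + 2/RR)}.

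| m (assumed) | f = 0: missed events unchanged | f = 0.5: half the gain is conversion | f = 1: all the gain is conversion |
|---|---|---|---|
| 0.5 | 6.25/5.10 = 1.23; 77% | not possible (needs m ≥ 0.575) | not possible (needs m ≥ 1.15) |
| 1.15 | 6.90/5.75 = 1.20; 72% | 6.325/5.75 = 1.10; 26% | 5.75/5.75 = 1.00; 5% |
| 2.0 | 7.75/6.60 = 1.17; 67% | 7.175/6.60 = 1.09; 23% | 6.60/6.60 = 1.00; 5% |
| 3.0 | 8.75/7.60 = 1.15; 62% | 8.175/7.60 = 1.08; 21% | 7.60/7.60 = 1.00; 5% |
| 4.6 | 10.35/9.20 = 1.13; 54% | 9.775/9.20 = 1.06; 18% | 9.20/9.20 = 1.00; 5% |

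In the last column power is only the rejection rate under no difference. At m = 2.0, for example, usual care has 4.6 attended + 2.0 missed = 6.6, and the incentive arm has 5.75 attended + 0.85 missed = 6.6.

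**Step 3: the other readings.** If missed events are set aside, RR stays at 5.75/4.6 = 1.25. If they are subtracted, with m = 2.0 in both arms, RR is (5.75 − 2.0)/(4.6 − 2.0) = 3.75/2.6 = 1.44. The same charts could therefore yield 1.17, 1.25 or 1.44, depending on how one sentence of Table 1 is read.

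**The case against.** The strongest reply is that Table 1 speaks of *considering* these items, not of adding them. An abstractor has to read no-show and cancellation entries in order to tell them from attended contacts, so the wording fits exclusion as well as inclusion. The rest of the document points that way: attendance is the stated construct, the eligible list has no missed events, and a missed appointment can hardly meet a 5-minute minimum. This stands. A reader might infer that Table 1 definitely counts missed events, or that no abstractor could satisfy both places. The text supports neither, because counting attended contacts and using missed entries only to exclude them satisfies both. The reply does not remove the problem, however. Table 1 is the designated detailed definition, it gives no rule for the missed items, and its 5-minute sentence covers synchronous interactions only, so it does not expressly rule a no-show out. This is also more than detail that an article leaves to a fuller document: the article states a calculation, and that calculation names events that its own definition leaves out.

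A second reply is that exact cancellation depends on assumptions. That is also right. It needs missed events to be added and the entire gain to be conversion, and nothing in the document says that the incentive works mainly in this way.

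A reader might also infer that texts and emails can inflate the count freely, or that the two 5-minute statements conflict. The document does not support this. Contacts must relate to the care plan, social or trivial contacts are excluded, and the chart review is blinded. Both 5-minute statements can be read as applying to live interactions, with email and text handled separately.

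**Conclusion.** The point holds as an unresolved inconsistency in the definition of the sole primary outcome. Table 1 brings missed events into the calculation without a rule, while Study Design and Quantitative Measures define the outcome as attendance.

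If missed events are added and the incentive does not change them, a true rate ratio of 1.25 becomes about 1.23 to 1.13, with power of 77% to 54%. If half the gain is conversion, it becomes 1.10 to 1.06, with power of 26% to 18% (m from 1.15 to 4.6). If all of it is conversion, it is 1.00. It would be too strong to say that the planned outcome cancels the effect; that is the extreme case of one possible reading.

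These figures rest on the assumed range for m, on taking the planning rate of 4.6 as attended contacts, and, for power, on the plan's own basis of one month of exposure and no overdispersion. The rate ratios do not depend on that last assumption.

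**What to change.** Amend the Service engagement row of Table 1 so that only completed eligible health-care contacts, as described in Quantitative Measures, enter the primary count. State that no-shows, cancellations and drop-outs are abstracted as separate items and reported descriptively by arm. Use the same wording in Quantitative Measures, and in Primary Outcome Analysis define total contacts as that count. Confirm that the planning rate of 4.6 per month was counted on the same basis; if it was, 67 per group and 172 in total are unchanged.

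The cost is a short text edit and separate fields on the abstraction form, with no new data source and no change to the model. It should be dated before the end-of-study chart review begins. On the article's timeline, follow-up data collection is still running.
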